### Selection method

A randomized sample of the population assigned and obtained through the SIAP (Primary Care Information System), will be stratified in proportion to the population assigned to each of the Primary Care teams participating in the study. It should be pointed out that the population assigned is practically equivalent to the updated municipal pattern.

### Phase I

The resulting variable is the ultrasonographic diagnosis of fatty liver. The diagnosis of fatty liver will be established according to the standard criteria accepted by the American Gastroenterology Association [21]: An increase in hepatic echogenicity taking renal echogenicity as a reference, the presence of enhancement and lack of differentiation in periportal intensity and the vesicular wall due to great hyperechogenicity of the parenchyma. The degree of involvement will be standardized with a semiquantitative scale of the degree of hepatic enhancement.

The following covariables will be evaluated in the study subjects:

1. Sociodemographic variables: age, sex, occupation, education and place of residence.

2. Clinical history including:

2.1 Personal history of: liver disease, biliary lithiasis, surgical interventions.

2.2 Presence of comorbidities: obesity and being overweight, type 2 diabetes, dyslipemia and arterial hypertension.

2.3 Alcohol intake: determine the type and quantity of beverages consumed.

2.4 Smoking habit.

2.5 Habitual drug use: history of drug use during the previous six months.

3. Physical examination:

3.1 Antropometric data: weight, height, abdominal obesity and body mass index.

3.2 Determination of arterial pressure.

4. Analytical determinations:

4.1 Blood analysis including: a complete hemogram, glycaemia, glycosylated haemoglobyn, urea, creatinine, uric acid, a lipid study (cholesterol, triglycerides, HDL, LDL) and liver function tests, including hepatitis markers (surface antigen of the hepatitis B virus and antibodies versus the hepatitis C virus).

4.2 Baseline insulin levels will be determined by the immunochemoluminescence method.

4.3 Determination of insulin resistance will be estalished with the HOMA method (homeostasis model assessment). ([glycaemia(mmol/L)/insulin (mU/L)]/22.5).

4.4 A sample of the first urine in the morning will be taken to determine microalbuminuria.

5. Determination of the HAIR score [17].

6. Diagnosis of the metabolic syndrome: This will be made according to the criteria of the WHO [18] modified by the European Group for the Study of Insulin Resistance [20], and the National Cholesterol Education Program (NCEP) [19].

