More recently a population study has been published including 420 patients diagnosed with fatty liver not related to alcohol from 1980 to 2000 in different primary, secondary and tertiary healthcare centres in Minnesota. The authors precisely defined the morbidity and mortality associated with this disease. The patients had a mean age of 49 years, two out of three were obese and had hypertriglyceridemia, 36% were hypertensive, 26% had diabetes and 36% presented altered baseline glycaemia. The mean follow up of the patients was of 8 years. During this time period 13% of the patients died, representing a mortality greater than that expected in the general population (RR 1.34; p = 0.03). On multivariate analysis, the predictive factors of mortality were age, the presence of cirrhosis and surprisingly, altered baseline glycaemia. Liver disease constituted the third cause of death in these patients following neoplasms and ischaemic heart disease, in contrast with the general population in whom liver diseases are the thirteenth cause of death. Specifically speaking, during the follow up period, 5% of the patients were diagnosed with cirrhosis, 3% presented complications and 7 patients died in relation to their chronic liver disease (1.7%) [14].

The pathogenesis of non alcoholic fatty liver is only partially known, although it seems to be multifactorial. The most widespread pathogenic theory is that of the double impact in which the first is a resistance to peripheral insulin resulting in the accumulation of fat in the liver, and the second is chronic oxidative stress which leads to apoptosis and/or hepatocellular necrosis, inflammation and fibrosis [15,16].

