The metabolic syndrome is constituted by the presence of a series of factors within the same subject such as obesity, arterial hypertension, dyslipemia or glucose intolerance and has been on the rise in recent years. Several criteria are used to define the metabolic syndrome, with the most commonly used being those of the World Health Organization (WHO) [18] and those of the Adult Treatment Panel III (ATP-III) of the National Cholesterol Education Program (NCEP) [19]. The criteria of the WHO require the presentation of some alteration in carbohydrate metabolism, whether diabetes, abnormal glucose tolerance or resistance to insulin. Two of the following criteria must also be taken into account: arterial hypertension > 140/90 mm Hg, obesity (BMI = 30 Kg/m^2^), hypertriglyceridemia ≥ 150 mg/dL or cHDL values < 35 in males and < 40 in females and microalbuminuria ≥ 20 μg/min. This definition places great importance on alterations in carbohydrate metabolism and insulin resistance as the elements necessary for the diagnosis of the metabolic syndrome. However, the definition by the WHO requires the presence of an alteration in glycaemia and does not place importance on the presence on abdominal obesity which is important to define insulin resistance. For this reason the European Group for the Study of Insulin Resistance (EGIR) has proposed several changes in the definition of the WHO, such as the presence of obesity (waist perimeter ≥ 94 cm), fasting plasma insulin determination and altered fasting glycaemia [20]. The criteria of ATP-III of the NCEP are based on the presence of abdominal obesity (≥ 88 cm in women and ≥ 102 cm in males), hypertriglyceridemia (≥ 150 mg/dL), low cHDL plasma values (<35 mh/dL), arterial hypertension (≥ 130/85 mm Hg) and altered fasting glycaemia (≥ 110 mg/dL). The criteria of the ATP-III are more clinical and easier to apply than those of the WHO, but the results of several studies have shown that the ATP-III criteria overestimate the presence of the metabolic syndrome. On the other hand, the criteria of the ATP-III do not correlate with those using insulin resistance as the fundamental element of diagnosis. Given the importance of the metabolic syndrome in the diagnosis of non alcoholic fatty liver and the discrepancies between the two models, we believe it may be useful to analyze both models in all the subjects to determine wihch model best defines the metabolic syndrome.

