### Plan of analysis

Data will be introduced into an ACCESS type database and then analysed. The prevalence of fatty liver will be estimated with a confidence interval of 95%.

A descriptive univariate and bivariate statistical analysis will be performed, analysing the qualitative variables with chi-squared test and the quantitative variables with the Students-t- test. Statistical significance will be established at 5% for all the bivariate analyses and contrasts will be considered at a bilateral level. Multivariate analysis will also be undertaken with logistic regression models (dependent variable presence/absence of fatty liver) allowing adjustment of the effect of the different independent variables on the presence of non alcoholic fatty liver.

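### The insulin-resistance index is printed as glycaemia divided by insulin; as written, the HOMA covariable falls as insulin rises and does not measure resistance

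*Protocol article*

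**What the plan says.** The covariables in the Phase I section open with "The following covariables will be evaluated in the study subjects". Glycaemia is part of the blood analysis in item 4.1. For insulin, item 4.2 says "Baseline insulin levels will be determined by the immunochemoluminescence method". Item 4.3 then defines the derived index: "Determination of insulin resistance will be estalished with the HOMA method (homeostasis model assessment). ([glycaemia(mmol/L)/insulin (mU/L)]/22.5". The operator between glycaemia and insulin is a slash, and the brackets, units and constant are intact. The article gives no other HOMA formula, no HOMA cut-off and no correction.

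The Plan of analysis provides for t-tests on quantitative variables and for logistic regression on the presence of fatty liver, "allowing adjustment of the effect of the different independent variables on the presence of non alcoholic fatty liver". It does not list the model terms by name.

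The Background describes the leading theory of pathogenesis as a double impact, in which "the first is a resistance to peripheral insulin resulting in the accumulation of fat in the liver".

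**The concern.** An index of insulin resistance should rise when more insulin accompanies a given glucose level. The printed quotient does the opposite: among subjects with equal glucose, the one with the highest insulin gets the lowest score. The theory cited in the Background leads one to expect resistance to go with fatty liver. A covariable coded as printed could therefore show resistance as protective, or show little association, purely because of the arithmetic. HOMA is the only index for which the Methods give an explicit resistance formula, so a programmer who follows the text has nothing else to check against.

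**Working it through.** **Inputs.** The printed formula is from Phase I, item 4.3. The article gives no HOMA value to reproduce and no distribution for glucose or insulin. All values of G (glucose, mmol/L) and I (insulin, mU/L), and all SDs below, are therefore assumptions.

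**Step 1: the two forms at example values.** Printed: (G / I) / 22.5. Product: (G × I) / 22.5.

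| G | I | Printed | Product |
|---|---|---|---|
| 4.5 | 5 | 0.0400 | 1.00 |
| 5 | 5 | 0.0444 | 1.11 |
| 5 | 10 | 0.0222 | 2.22 |
| 5 | 20 | 0.0111 | 4.44 |
| 6 | 20 | 0.0133 | 5.33 |
| 7 | 30 | 0.0104 | 9.33 |

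In the three rows with G = 5, each doubling of insulin halves the printed index and doubles the product. This holds at any fixed glucose and needs no assumption.

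**Step 2: the constant.** 22.5 = 4.5 × 5, so it scales a product to exactly 1 at G = 4.5 and I = 5. In the quotient the same subject scores 0.04, and 22.5 has no comparable role. The constant points to a product.

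**Step 3: how the two forms rank subjects.** Let sG and sI be the SDs of ln G and ln I, and r their correlation. For log-normal values,

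corr(ln G + ln I, ln G − ln I) = (sG² − sI²) / √[(sG² + sI²)² − 4 r² sG² sI²].

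The sign is that of sG² − sI². The indices run in opposite directions when ln insulin varies more than ln glucose, and in the same direction when it varies less.

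Take sG = 0.12 and sI = 0.55. The numerator is 0.0144 − 0.3025 = −0.2881.

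- r = 0.2: denominator √(0.10043 − 0.00070) = 0.3158, correlation −0.91.
- r = 0.6: denominator √(0.10043 − 0.00627) = 0.3068, correlation −0.94.

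Converting by Spearman = (6/π) arcsin(ρ/2) gives −0.90 and −0.93. A simulation of 200,000 pairs gave −0.90, −0.92 and −0.93 for r = 0.2, 0.4 and 0.6.

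**Step 4: direction of the association with fatty liver.** A second simulation (400,000 subjects per scenario) let one latent resistance factor raise ln glucose, ln insulin and the odds of fatty liver. The table shows the mean log index in subjects with fatty liver minus that in subjects without.

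| SD ln G | SD ln I | Printed | Product |
|---|---|---|---|
| 0.08 to 0.25 | 0.3 to 0.7 | −0.349 to −0.015 | +0.124 to +0.538 |
| 0.5 | 0.7 | −0.111 to −0.063 | +0.389 to +0.678 |
| 0.5 | 0.5 | about 0 (+0.003) | +0.328 to +0.560 |
| 0.5 | 0.3 | +0.069 to +0.112 | +0.266 to +0.450 |

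The printed form reverses the sign wherever insulin is the more variable of the two. It loses the association when the SDs are equal, and keeps a weaker positive one when glucose is the more variable. The product form is positive throughout.

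**The case against.** The best defence is that item 4.3 names the HOMA method, so the slash may be a drafting slip in a condensed article that the analysts would not follow. That is plausible but cannot be confirmed. The formula is stated in the Methods and nothing in the article corrects it, so it has to be judged as printed.

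The other objections limit the consequences, and they stand. A reader might infer four things that the article does not support:

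- **That the association will certainly reverse.** The sign depends on the relative spread of ln insulin and ln glucose, and the article gives neither.
- **That resistant subjects will be classified as non-resistant.** No HOMA cut-off is stated, so there is no classification rule to invert.
- **That the metabolic syndrome diagnosis is corrupted.** The Background says of the WHO criteria "This definition places great importance on alterations in carbohydrate metabolism and insulin resistance as the elements necessary for the diagnosis of the metabolic syndrome", which makes the link tempting. The same section, however, accepts diabetes or abnormal glucose tolerance as alternatives to insulin resistance. For the European modification it lists fasting insulin, not HOMA, and the NCEP criteria it gives contain no resistance item. Item 6 of Phase I does not refer to item 4.3.
- **That the study rests on insulin resistance as an established mechanism.** The Background calls the pathogenesis only partly known and presents insulin resistance as part of the most widespread theory.

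The main prevalence estimate has an ultrasound outcome, and the sample size rests on the precision of a proportion. The HAIR score has its own definition of insulin resistance in the Background, built on diabetes or glycaemia together with blood pressure, lipid and anthropometric criteria. None of these uses HOMA.

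**Conclusion.** The formula is wrong as written. That the printed index falls as insulin rises at fixed glucose is exact and assumption-free, and it is enough to show that the covariable would not measure insulin resistance. The effect on the association with fatty liver is conditional. Reversal is expected if ln insulin varies more than ln glucose, with a rank correlation of about −0.9 between the two forms at assumed SDs of 0.55 and 0.12. Otherwise the association is attenuated towards zero or stays weakly positive.

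The damage is confined to HOMA wherever it enters the bivariate and logistic analyses. It extends to the metabolic syndrome diagnosis only if HOMA is used for the resistance criterion, which the article does not say.

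**What to change.** In Phase I, item 4.3, replace the formula with [glycaemia (mmol/L) × insulin (mU/L)] / 22.5. Check that the derivation in the study database multiplies, for instance by confirming that glucose 5 mmol/L and insulin 5 mU/L return 1.11. Use the corrected index wherever HOMA enters the analyses, including the metabolic syndrome criterion if HOMA is used there.

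The cost is one operator in the text and one check of the derived variable. Glucose and insulin are already measured in the study subjects, so the index can be recomputed without new data.

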### Phase II

Patients with diagnosed liver disease will receive the normal control and follow up by their reference physician. Patients with fatty liver with no evidence of liver disease will be advised to modify their habits and risk factors and will initiate annual control and ultgrasonographic follow up. The resulting variable in this phase will be the persistence, reversal or progression of liver involvement. This subgroup of subjects will provide a cohort of patients to obtain data on the natural history of the disease in future studies.

### Plan of analysis

Data will be introduced into an ACCESS type database and then analysed. The prevalence of fatty liver will be estimated with a confidence interval of 95%.

A descriptive univariate and bivariate statistical analysis will be performed, analysing the qualitative variables with chi-squared test and the quantitative variables with the Students-t- test. Statistical significance will be established at 5% for all the bivariate analyses and contrasts will be considered at a bilateral level. Multivariate analysis will also be undertaken with logistic regression models (dependent variable presence/absence of fatty liver) allowing adjustment of the effect of the different independent variables on the presence of non alcoholic fatty liver.

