### Sample size

With an alpha risk of 0.05 for a precision of ± 0.03 percentage units in a bilateral contrast for an estimated proportion of 0.20 a randomized sample proportional to 683 subjects is required. Considering that 15% of the population will present alcohol intake or some previous liver disease, the number of patients to study in this percentage is increased making a total of 786 individuals necessary to fulfil the final sample size.

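### At the implied split of about 137 v 546, Student's t-test in its usual equal-variance form holds its 5% level only if the two groups have equal SDs; naming Welch's test removes that condition (minor)

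*Protocol article*

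**What the plan says.** The Plan of analysis announces a descriptive univariate and bivariate analysis. It sends categorical variables to the chi-squared test and "the quantitative variables with the Students-t- test". It then sets one level for all of them: "Statistical significance will be established at 5% for all the bivariate analyses", and "contrasts will be considered at a bilateral level". No unequal-variance version, transformation or rank test is mentioned. The same section says that "The prevalence of fatty liver will be estimated with a confidence interval of 95" per cent, and it takes adjusted effects from logistic regression with presence or absence of fatty liver as the dependent variable.

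The group sizes follow from the Sample size section: "for an estimated proportion of 0.20 a randomized sample proportional to 683 subjects is required".

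The Phase I section lists the continuous measurements that would go through the t-test. They include glycaemia, lipids, uric acid, liver function tests, insulin ("Baseline insulin levels will be determined by the immunochemoluminescence method") and the HOMA index.

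**The concern.** The equal-variance t-test pools the two group variances, weighted by group size. With about four subjects without fatty liver for each subject with it, the pooled variance mostly reflects the larger group, whereas the uncertainty of the difference in means comes mostly from the smaller group. If the smaller group is the more variable, the standard error is too small and the test rejects too often. If it is the less variable, the test rejects too seldom.

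Sample size protects a t-test against non-normality but not against this, because the bias depends on the ratio of the group sizes and the ratio of the SDs. At stake is the calibration of the unadjusted p-values that describe how subjects with fatty liver differ from those without (the second main objective, and any unadjusted look at continuous components under the third).

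**Working it through.** **Inputs.** From the Sample size section: expected proportion 0.20, precision ±0.03, two-sided alpha 0.05, 683 evaluable subjects. From the Plan of analysis: Student's t-test, two-sided 5%. The two groups are taken to be fatty liver present and absent, the outcome of the logistic model. The SD ratio r (fatty liver/other) is not in the article and is an assumption, shown as a range on both sides of 1.

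**Plan's own figure.** n = 1.96² × 0.20 × 0.80 / 0.03² = 682.9, rounded up to 683. The stated figure reproduces.

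**Group sizes.** 0.20 × 683 = 136.6, so about 137 with fatty liver and 683 − 137 = 546 without.

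**True level of the equal-variance test when the means are equal.** With the SD of the larger group set to 1:

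- SE² used by the test = [(136 r² + 545)/681] × (1/137 + 1/546)
- True SE² = r²/137 + 1/546
- True level ≈ 2 × [1 − Φ(1.963 × SE used / true SE)], where 1.963 is the critical value on 681 degrees of freedom

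Example, r = 1.5: SE² used = (851/681) × 0.009131 = 0.01141; true SE² = 0.01642 + 0.00183 = 0.01825; the ratio of SEs is √(0.01141/0.01825) = 0.791. The level is 2 × [1 − Φ(1.552)] = 12.1%.

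| Assumed SD ratio (fatty liver/other) | SE used / true SE | True two-sided level |
|---|---|---|
| 0.8 | 1.142 | 2.5% |
| 1.0 | 1.000 | 5.0% |
| 1.25 | 0.876 | 8.5% |
| 1.5 | 0.791 | 12.1% |
| 2.0 | 0.686 | 17.8% |

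A simulation with normal data (40,000 runs per ratio) gave 4.8%, 8.6%, 12.0% and 18.0% for Student's test at ratios 1.0, 1.25, 1.5 and 2.0. Welch's test gave 4.8% to 5.1% at these ratios and at 0.67.

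**Where the inflation does not arise.** Suppose a variable is log-normal with the same log-SD in both groups, so that its SD rises only because its mean rises. Under the null hypothesis the means are equal and so are the SDs. Simulations at 137 v 546 with log-SD 0.6 or 0.8 and a geometric mean ratio of 1.0 gave Student's test a level of 4.6% to 5.1%, and Welch's 5.0% to 5.6%. The inflated levels in the table therefore need similar means with different spreads.

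**Log scale.** For an assumed log-SD of 0.8 and geometric mean ratio of 1.2, simulated power (20,000 runs) is about 55% with Student's test on the raw scale and 66% on the log scale. In the same simulation, Welch's test on the raw scale has about 47%.

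**The case against.** The strongest reply has four parts.

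1. **Nothing in the article shows that the SDs differ.** This stands. A reader might infer that the fatty-liver group must be the more variable, since the Background section reports a cohort with 26% diabetes and 36% altered baseline glycaemia, and a mixed group has a wider spread. That makes the direction plausible for some variables. But the article gives no SD for either group and no matching figures for subjects without fatty liver. The direction remains an assumption, and with the reverse ratio the test is conservative.

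2. **Skewness alone does not break the level.** This also stands. If the SD rises only with the mean, the SDs are equal under the null and the 5% holds, as the log-normal check shows.

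3. **The article does not write pooled or equal variance, and a condensed article may leave the version to the full plan.** This stands in part. The article is not silent: it names a test whose usual meaning is the equal-variance one, and it attaches a level to it. If the full plan already uses the unequal-variance version, naming it settles the point.

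4. **The consequences are small.** This stands. The comparisons are called descriptive, the metabolic-syndrome components are largely defined by thresholds and so go to the chi-squared test, and adjusted effects come from logistic regression.

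A reader might also infer that the plan's 95% confidence interval would be wrong. It would not: the only interval stated is for the prevalence, which does not use the t-test, and no interval for a difference in means is announced.

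**Conclusion.** The point holds as a conditional and minor one. Read in its usual sense, the named test delivers the stated 5% at 137 v 546 only when the group SDs are equal. Over assumed SD ratios from 0.8 to 2.0 the true level runs from 2.5% to 17.8%, on both sides of the nominal value.

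This rests on three assumptions: the equal-variance reading of Student's test, a split close to the plan's own 20% of 683, and variables whose spreads differ while their means are similar. The article neither confirms nor excludes the last. What is shown is that the level depends on a condition the plan does not need to impose, not that the plan's error rates fail.

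**What to change.** In the Plan of analysis, replace Student's t-test with Welch's (unequal-variance) t-test for the quantitative variables. This changes one phrase and needs no new data. If the variances prove equal, almost nothing is lost.

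Optionally, add that clearly right-skewed variables (triglycerides, insulin, HOMA, transaminases) are analysed on the log scale, with results given as geometric mean ratios. This raises power in the setting shown above, and it avoids the lower raw-scale power of Welch's test when the smaller group has the higher mean. Its cost is that it compares geometric rather than arithmetic means, so the choice should be made before the data are seen.
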